| **Is statistical expertise available within the research team?**  *If yes, please indicate the name(s) of the relevant investigator(s)*  [name] |  |  |
| **Is experience of handling large data sets (>1 million records) available within the research team?**  *If yes, please indicate the name(s) of the relevant investigator(s)*  [name] |  |  |
| **Is experience of practising in UK primary care available within the research team?**  *If yes, please indicate the name(s) of the relevant investigator(s)*  [name] |  |  |
| 1. **References relating to your study**   Please list up to 3 references (most relevant) relating to your proposed study:  Rybniker J, Vocat A, Sala C, Busso P, Pojer F, Benjak A, Cole ST 2015 Lansoprazole is an antituberculous prodrug targeting cytochrome bc1. Nat Commun. Jul 9;6:7659. doi: 10.1038/ncomms8659.  Zenner D, Kruijshaar ME, Andrews N, Abubakar I. 2012. Risk of tuberculosis in pregnancy: a national, primary care-based cohort and self-controlled case series study. Am J Respir Crit Care Med. 185(7):779-84. doi: 10.1164/rccm.201106-1083OC. | | |
| **Section C: Access to the data** | | |
| 1. **Financial Sponsor of study**   Pharmaceutical Industry  *Please specify:*      Academia  *Please specify:*LSHTM  Government / NHS  *Please specify:*      Charity *Please specify:*  Other  *Please specify:*      None | | |
| 1. **Type of Institution carrying out the analyses**   Pharmaceutical Industry *Please specify:*      Academia *Please specify:*LSHTM  Government Department *Please specify:*      Research Service Provider *Please specify:*  NHS *Please specify:*      Other  *Please specify:* | | |

| 1. **Data source**   The sponsor has direct access to CPRD GOLD and will extract the relevant data*    A data set will be supplied by CPRD**  CPRD has been commissioned to extract the relevant data and to perform the analyses  Other *Please specify:*    *If data sources other than CPRD GOLD are required, these will be supplied by CPRD  ** Please note that datasets provided by CPRD are limited in size. Applicants should contact CPRD ([[contact]](mailto:[contact])) if a dataset of >300,000 patients is required. |
| --- |
| 1. **Primary care data** (please specify which primary care data set(s) are required)   Vision only (Default for CPRD studies)  EMIS® only*  Both Vision and EMIS®*  *Note: Vision and EMIS are different clinical systems, Vision data has traditionally been used for CPRD, EMIS is currently undergoing beta-testing.*  **Investigators requiring the use of EMIS data must discuss the study with a member of CPRD staff before submitting an ISAC application*  Please list below the name of the person/s at the CPRD with whom you have discussed your request for EMIS data: |
| **Section D: Data linkage** |
| 1. **Does this protocol also seek access to data held under the CPRD Data Linkage Scheme?**   Yes*  No  If No, please move to section E.  **Investigators requiring linked data must discuss the study with a member of CPRD staff. It is important to be aware that linked data are not available for all patients in CPRD GOLD, the coverage periods for each data source may differ and charges may be applied. Please contact the CPRD Research Team on [contact] or email* [*[contact]*](mailto:[contact]) *to discuss your requirements before submitting your application.*  Please list below the name of the person/s at the CPRD with whom you have discussed your request:  [name]  *Please note that as part of the ISAC review of linkages, the protocol may be shared - in confidence - with a representative of the requested linked data set(s) and summary details may be shared - in confidence - with the Confidentiality Advisory Group of the Health Research Authority.* |

| 1. **Please select the source(s) of linked data being requested:**   ONS Mortality Data  NCDR Cancer Registry Data*  Inpatient Hospital Episode Statistics  MINAP  Outpatient Hospital Episode Statistics  Mother Baby Link    Index of Multiple Deprivation  Townsend Score  Other** *Please specify:*  **Please note that applicants seeking access to cancer registry data must provide consent for publication of their study title and study institution on the UK Cancer Registry website. They must also complete a* ***Cancer Dataset Agreement Form*** *(available from CPRD) and provide a* ***System level Security Policy*** *for each organisation involved in the study.*  *** If “Other” is specified, please name an individual in CPRD that this linage has been discussed with.* |
| --- |
| 1. **Total number of linked datasets requested including CPRD GOLD**: 3 |

**Protocol Section**

The following headings **must** be used to form the basis of the protocol. Pages should be numbered. All abbreviations must be defined on first use.

1. **Lay Summary (Max. 200 words)**

A recent study demonstrated that in laboratory tests, lansoprazole appears to have potent activity against tuberculosis. Lansoprazole belongs to a class of drugs called proton pump inhibitors and is widely used to treat stomach disorders such as heartburn. It hasn’t previously been thought to have any antibiotic properties and is not used to treat infections. Other members of the proton pump inhibitor drug class were not found to have similar properties against tuberculosis. We propose a cohort study, comparing the risk of tuberculosis disease amongst people taking lansoprazole with people taking other proton pump inhibitors. If the results of the laboratory experiments have a useful clinical application, we would expect people taking lansoprazole to have a lower rate of TB. Our findings will be the first clinical evidence of the effect of lansoprazole on active tuberculosis and will help determine whether lansoprazole may be worth investigating further for this indication.

1. **Technical Summary (Max. 200 words)**

Our overall aim is to assess the effect of lansoprazole on the risk of tuberculosis disease. In order to achieve this we will estimate the relative risk of tuberculosis comparing people prescribed lansoprazole with people prescribed omeprazole or pantoprazole. We will construct a cohort of new users of lansoprazole and new users of omeprazole or pantoprazole and use Cox regression to estimate the hazard ratio for tuberculosis disease.

1. **Objectives, Specific Aims and Rationale**
2. *Aim*

To assess the effect of lansoprazole on the risk of tuberculosis (TB) disease.

1. *Objectives*

To estimate the relative risk of TB comparing people prescribed lansoprazole with people prescribed omeprazole or pantoprazole.

1. *Rationale*

By demonstrating whether the rate of TB disease is lower in people taking lansoprazole compared with omeprazole or pantoprazole we will be able to see whether this drug may be worth investigating further for clinical benefit against TB.

1. **Background**

Rybniker et al1 recently used an intracellular assay procedure to screen for drugs with antituberculous potential. They found that lansoprazole was highly active against TB in cell culture, when transformed intracellularly from the prodrug lansoprazole to lansoprazole sufoxide. Strong activity was also found against drug-resistant TB clinical isolates suggesting further clinical investigation is warranted. Of note, other PPIs (omeprazole and pantoprazole) were not found to have anti-tuberculous activity. To date there have been no clinical studies assessing whether lansoprazole as used in routine clinical care has such anti-tuberculous properties. Given the widespread use of PPIs over many years, we believe the CPRD provides an ideal opportunity to investigate whether lansoprazole may be associated with a lower risk of TB disease by making a direct comparison between lansoprazole users and users of omeprazole or pantoprazole.

1. **Study Type**

This is a hypothesis testing study

1. **Study Design**

This will be a cohort study comparing the rate of TB disease in people treated with lansoprazole, compared with people treated with omeprazole or pantoprazole. This design will minimise confounding because both lansoprazole exposed and unexposed patients will be receiving a PPI and will therefore have similar underlying health problems which may be associated with the risk of TB disease.

1. **Sample Size**

A feasibility count from Jan 2015 CPRD GOLD indicates the following:

- Lansoprazole new users n=744,144
- Omeprazole and pantoprazole new users n=1,182,888
- Lansoprazole new users with subsequent TB n=1,227

At this stage we cannot be sure how many incident TB cases will occur during PPI exposure, rather than after exposure has ended. Nor can we state with confidence what effect size we expect to detect. Table 1 therefore gives estimates of power under a range of assumptions, based on a conservative 1:1 comparison between lansoprazole and omeprazole or pantoprazole.

|  | *Number of exposed cases* | | | |
| --- | --- | --- | --- | --- |
| *Relative Risk* | **1,200** | **800** | **500** | **200** |
| **0.9** | 0.73 | 0.56 | 0.38 | 0.18 |
| **0.8** | >0.99 | >0.99 | 0.94 | 0.61 |
| **0.7** | >0.99 | >0.99 | >0.99 | >0.99 |
| **0.6** | >0.99 | >0.99 | >0.99 | >0.99 |
| **0.5** | >0.99 | >0.99 | >0.99 | >0.99 |

Table 1: Estimates of power to detect a range of possible relative risks, under a range of assumptions about the number of likely lansoprazole exposed TB cases

For most of the assumptions tested, we will have adequate power to detect an association with lansoprazole assuming a protective association of 0.8 or greater, which we believe would represent a clinically relevant effect size.

1. **Data Linkage Required (if applicable)**

Patient-level index of multiple deprivation data are required to assess for confounding as it is likely that risk of TB will vary by socioeconomic status. Since this is only available for patients in the linkage scheme, we propose to use practice-level index of multiple deprivation for the remainder of patients (rescaled to be on the same scale as the patient level scores, using observations where both are available). We have used this strategy successfully in previous CPRD studies.

We will also use HES (in- and out-patient data) to identify cases of TB recorded in hospital.

1. **Study Population**

The source population for this study is all patients aged 16 years or over with acceptable user status registered in the entire CPRD, with up-to-standard (uts) follow up of at least 12 months.

From the source population we will select all patients who are:

1. New users of lansoprazole; defined as people starting treatment with lansoprazole after at least 12 months uts follow up, with no previous record of receiving a PPI.
2. New users of omeprazole or pantoprazole; defined as people starting treatment with omeprazole or pantoprazole after at least 12 months uts follow up, with no previous record of receiving a PPI.

Exposure to lansoprazole, omeprazole and pantoprazole will be defined by prescription records, as conducted previously by this research group2.

All patients with a record of TB disease prior to their first PPI will be excluded from the study.

1. **Selection of comparison group(s) or controls**

All new users of omeprazole and pantoprazole are to be included as the comparator group, as described in Section I above. Users of a PPI are likely to be more sick than people not using PPIs, and therefore may be at an increased risk of outcomes such as acquiring an infection. Omeparazole and pantoprazole exposed people are therefore the ideal comparator group as we assume that the choice of specific PPI is less likely to be related to underlying health, and both were found to have no effect on TB in the study that motivated this work. Other PPIs were not investigated by Rybniker et al and so have not been included here. We believe it is very unlikely that PPI choice is related to the future risk of TB.

1. **Exposures, Outcomes and Covariates**

For PPI exposure, we will use recorded information on intended treatment duration and dosage instructions to estimate likely exposure duration. Where duration is missing, we will impute the population median exposure length. From past experience of PPI prescribing in CPRD, the majority of prescriptions last 30 days.

For the outcome, we will select all clinical records indicating TB as identified using codes in Appendix 1. Our primary outcome will be defined as all codes indicating TB disease. The earliest recorded date of a code indicating the outcome will be taken as the date of TB disease. A previous study using a similar approach for TB case identification in CPRD found incidence rates comparable to Public Health England figures, suggesting reliable case ascertainment3. However, the time between TB infection and diagnosis with TB disease is known to involve a median delay of 1.26 years, but with substantial variability4 and so the aetiologically relevant exposure for a protective effect to be seen is likely to be some time earlier than the recorded diagnosis. For this reason, all TB dates will be moved earlier by 12 months in the primary analysis. As sensitivity analyses, TB dates will be defined as 1) as recorded in CPRD, 2) 2 years earlier than recorded and 3) 5 years earlier than recorded. In all analyses where the TB date is moved earlier, follow up time for both TB cases and non-cases will be censored the same amount of time earlier.

CPRD linked Hospital Episodes Statistics (HES) in- and out-patient data will also be searched for codes indicating tuberculosis (A15-A19). A sensitivity analysis restricted to the CPRD HES-linked practices and time periods will be conducted, taking the earliest of CPRD or HES identified TB disease.

Covariates to be explored for their potential confounding nature will be age, sex, calendar year, smoking behaviour, body mass index, alcohol use, ethnicity, drug abuse, the use of inhaled/oral corticosteroids, travel vaccines, antimalarials, diabetes, rheumatoid arthritis, irritable bowel disease, chronic obstructive pulmonary disease, asthma, chronic kidney disease, depression, leukaemia, lymphoma, myeloma any record signifying the use of chemotherapy, a record of HIV infection and index of multiple deprivation score. Of note, ciclosporin and tacrolimus, both immunosuppressive drugs, are known to interact with omeprazole but not other PPIs. It is possible that people at higher risk of TB will therefore be given PPIs other than omeprazole and for this reason, patients with a history of use of either drug will be excluded from the study population.

1. **Data/ Statistical analysis**

Each participant’s follow up time will begin at the first prescription for lansoprazole or omeprazole/pantoprazole. All subsequent time will be classified as one of the following

- *Lansoprazole exposed* – all time covered by lansoprazole prescriptions, including a 60 day period after the estimated end of treatment date, to allow for stock piling and non-adherence
- *Omeprazole/pantoprazole exposed* – all time covered by omeprazole/pantoprazole prescriptions including a 60 day period after the estimated end of treatment date, to allow for stock piling and non-adherence. This will be the baseline against which other exposures are compared.
- *Unexposed* – all time between lansoprazole/omeprazole/pantoprazole exposure periods, or between the end of PPI exposure and the end of follow up. This time is being handled separately as it is plausible that a period of time off a PPI may be a marker of important changes in underlying health, with an associated change in the risk of TB disease

Where patients switch directly between one PPI and another, exposure will be updated to the new PPI from the date it is prescribed, assuming stock-piled drug is no longer taken.

End of follow up will be defined as the earliest of first recorded TB disease, death, transfer away, end of UTS or last data collection date.

Examples of how patient follow up time will be allocated are shown in Figure 1.

*Figure 1: Example Patient Exposure Timelines*

1. Lansoprazole exposure only

12 months follow up with no PPI

End uts

Lansoprazole prescription

EXPOSURE GROUP

Lanoprazole

1. Omeprazole or pantoprazole only

12 months follow up with no PPI

End uts

Omeprazole prescription

EXPOSURE GROUP

Omeprazole

or pantoprazole

1. Lansoprazole and omeprazole/pantoprazole

12 months follow up with no PPI

End uts

Lansoprazole prescription

Omeprazole prescription

EXPOSURE GROUP

Lansoprazole

Omeprazole

or pantoprazole

4. Lansoprazole with Breaks

12 months follow up with no PPI

End uts

Lansoprazole prescription

EXPOSURE GROUP

Lansoprazole

Unexposed

5. Lansoprazole, omeprazole/pantoprazole and breaks

12 months follow up with no lansoprazole

End uts

Pantoprazole prescription

Lansoprazole prescription

EXPOSURE GROUP

Lansoprazole

Unexposed

Omeprazole

or pantoprazole

The primary comparison of interest is the risk of TB comparing lansoprazole exposed time with omeprazole or pantoprazole exposed time. People starting treatment with omeprazole or pantoprazole but later receiving lansoprazole will transition to the lansoprazole group at that time and vice versa. Follow up for each patient will end at the earliest of; TB disease, transfer out, death or end of uts follow up.

Descriptive analyses will be performed, comparing the distribution of the following variables between patients starting lansoprazole and those starting omeprazole/pantoprazole: Age, sex, calendar year, smoking behaviour, body mass index, alcohol use, ethnicity, drug abuse, the use of corticosteroids, any record signifying any prior use of chemotherapy, travel vaccines, antimalarials, diabetes , rheumatoid arthritis, irritable bowel disease, chronic obstructive pulmonary disease, asthma, chronic kidney disease, depression, leukaemia, lymphoma, myeloma, a record of HIV infection and index of multiple deprivation score.

Cox regression will be used to estimate hazard ratios and 95% confidence intervals, comparing lansoprazole exposed time against omeprazole or pantoprazole exposed time. A crude model will be constructed with just the main exposure variable, followed by a model adjusting for potential confounders.

We will fit an interaction term to look for effect modification between lansoprazole exposure and age.

As a sensitivity analysis we will vary the time following the end of estimated treatment duration after which therapy cessation is assumed, from 60 to 90 days. A further sensitivity analysis will censor all patients after a cessation or switch of PPI therapy, (cessation defined as longer than 60 days not covered by a prescription.)

1. **Plan for addressing confounding**

Potentially confounding variables have been selected based on their possible association with the risk of TB, as listed in part K. These variables will be explored and potentially adjusted for in a multivariable Cox regression model. However, we believe substantial confounding is unlikely in this study as risk factors for TB are not expected to be associated with the choice of specific PPI, with the exception of calendar year. It is possible that rates of TB have changed over time and local prescribing guidance for preferred PPI has varied over the years mainly based on cost considerations. PPI preference could also be dictated by differential drug interactions between individual PPIs, as noted above for tacrolimus and ciclosporin and people with a history of taking either drug will be excluded.

1. **Plan for addressing missing data**

There is known missingness in the smoking and alcohol status and BMI variables. From previous experience of studies involving people taking long term medication such as PPIs it is expected that <10% of patients will have missing data. We plan to conduct a complete case analysis, which relies on the assumption that the probability of these data being missing is independent of TB risk, conditional on covariates5; given the small amount of missing data, any violation of the assumption is unlikely to importantly affect the results. Ethnicity is likely to have substantially more missing data. Again, we will conduct a complete case analysis with this variable included in the model, recognising the reduction in sample size will be greater and that this is a limitation of the study.

1. **Limitations of the study design, data sources and analytical methods**

It is possible that TB may go unidentified in some patients and therefore unrecorded in CPRD. Assuming this is non-differential between PPIs, this will only lead to a loss of power, rather than a biased estimate; however the power calculations we present are based on identified cases and so this is not expected to be a major limitation.

The timing of TB disease recorded in CPRD will not be the same as the date when infection actually occurred as we are detecting recorded diagnoses rather than actual time of infection. We are dealing with this by moving the date of TB disease to an earlier time and have planned sensitivity analyses varying the length of this time shift. However, PPI exposure tends to be for long periods in many patients and so it is not expected that timing inaccuracy for infection will have a substantial impact on the estimated exposure status of cases.

The recording of risk factors for TB is unlikely to be perfect. For example HIV status, drug abuse and exposure to chemotherapy may not be well recorded in primary care. However, we anticipate little confounding in this study, except by calendar time and possibly age, both of which are well recorded. Other possible sources of confounding we will be unable to address include clinical commissioning group, previous imprisonment and homelessness.

We anticipate that our estimate of PPI exposure times will be flawed to some extent due to lack of adherence. This will tend to lead to an underestimate of the effect size of any true association with lansoprazole, assuming the degree of exposure misclassification is non-differential in those people with and without subsequent TB disease.

As noted above, ethnicity will not be recorded for all patients and so the complete cases analysis including this variable may give a biased result. However, although ethnicity is a strong risk factor for TB, it is unlikely to be a strong deciding factor for specific PPI selection.

1. **Patient or user group involvement (if applicable)**

At this stage we do not plan to involve patients in the study; but depending on our findings it is possible we would seek patient engagement to help shape future research plans.

1. **Plans for disseminating and communicating study results, including the presence or absence of any restrictions on the extent and timing of publication**

All results will be presented at scientific conferences and published in a peer reviewed journal.

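### The comparator rests on users of either PPI having similar underlying health, but neither variable list records why the PPI was started or NSAID or antiplatelet use, so confounding by indication is not directly tested and only partly removed

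*Protocol*

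**What the plan says.** The Study Design section infers comparability from shared PPI use: "both lansoprazole exposed and unexposed patients will be receiving a PPI and will therefore have similar underlying health problems". The sentence goes on to say that those problems may be linked to TB risk. The section on selection of comparison groups describes PPI users as sicker than non-users and possibly more prone to infection, then states "we assume that the choice of specific PPI is less likely to be related to underlying health".

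The covariates are given as an explicit list in the Exposures, Outcomes and Covariates section. It opens "Covariates to be explored for their potential confounding nature will be age, sex, calendar year, smoking behaviour, body mass index, alcohol use, ethnicity" and continues with "the use of inhaled/oral corticosteroids, travel vaccines, antimalarials, diabetes, rheumatoid arthritis, irritable bowel disease, chronic obstructive pulmonary disease, asthma", then further comorbidities, cancers, chemotherapy, HIV and deprivation. The Data/Statistical analysis section repeats essentially the same variables for the baseline table, "comparing the distribution of the following variables between patients starting lansoprazole and those starting omeprazole/pantoprazole".

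The plan for addressing confounding gives the selection rule: "Potentially confounding variables have been selected based on their possible association with the risk of TB". It expects little confounding apart from calendar year. It allows that drug interactions may steer the choice of PPI, and handles this by excluding past users of ciclosporin or tacrolimus. The Limitations section names commissioning group, imprisonment and homelessness as confounders that cannot be addressed; PPI indication is not among them.

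The first Amendment reports that a protective association with TB was found and adds myocardial infarction (MI) as a control outcome. Amendment 2 reports no association with MI and adds herpes zoster.

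**The concern.** An active comparator removes confounding by indication only if the reasons for treatment are balanced between the drugs. A first PPI may be a short eradication course, gastroprotection alongside other drugs, or long-term reflux treatment, and such patients can differ in health. The protocol itself accepts that the problems behind PPI use may bear on TB. What remains is balance between the drugs, and on the reason for treatment this is assumed.

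If the mix of indications differs between the drugs and relates to TB beyond the listed covariates, the hazard ratio is biased. The baseline table would not show the difference in indication, and the adjusted model would correct only the part that runs through listed variables. In a cohort of this size, a modest bias can reach statistical significance. Because a protective association has already been reported, the check bears on how that result is read.

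**Working it through.** **1. The lists against the premise.** The documents state no figure for this point, so the first check is a reading of both lists.

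| Item | Covariate list | Baseline table |
|---|---|---|
| Reflux, peptic ulcer or dyspepsia | absent | absent |
| H. pylori eradication course | absent | absent |
| GI bleed or upper GI cancer | absent | absent |
| NSAID use | absent | absent |
| Antiplatelet use | absent | absent |
| Corticosteroids | present (inhaled/oral) | present |
| Rheumatoid arthritis (proxy for NSAID or steroid use) | present | present |
| Age, smoking, deprivation, COPD, diabetes, HIV and others | present | present |

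The absences follow from the selection rule, which looks to TB risk and not to the reason for the PPI. The protocol concedes interaction-driven choice of PPI but deals with two drugs only. Its own reference list includes a study of clopidogrel and its interaction with PPIs, yet antiplatelet use is in neither list.

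**2. Size on assumed inputs.** For one binary indication, with no drug effect:

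spurious HR = [1 + pL(R − 1)] / [1 + pO(R − 1)]

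Here pL and pO are its prevalences in lansoprazole and comparator users, and R is its TB rate ratio after adjustment for the listed covariates. All three are assumptions.

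| pL | pO | R = 1.2 | R = 1.5 | R = 2 | R = 3 |
|---|---|---|---|---|---|
| 10% | 15% | 0.99 | 0.98 | 0.96 | 0.92 |
| 20% | 25% | 0.99 | 0.98 | 0.96 | 0.93 |
| 10% | 20% | 0.98 | 0.95 | 0.92 | 0.86 |
| 20% | 40% | 0.96 | 0.92 | 0.86 | 0.78 |
| 20% | 10% | 1.02 | 1.05 | 1.09 | 1.17 |

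For 10% against 20%: at R = 2, 1.10/1.20 = 0.917; at R = 3, 1.20/1.40 = 0.857. The last row reverses the imbalance, and the bias then hides a protective effect.

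**3. Against the protocol's target.** The Sample Size section treats a relative risk of 0.8 as clinically relevant. On the log scale:

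- ln(0.917)/ln(0.8) = −0.087/−0.223 = 0.39
- ln(0.857)/ln(0.8) = −0.154/−0.223 = 0.69

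These two cases therefore account for about 40% to 70% of the target effect. Of the cases shown, only 20% against 40% with R = 3 (0.78) reproduces it alone.

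**4. Chance that such a bias is significant.** Power = Φ(|ln HR| × √E / 2 − 1.96), with E = 2 × the exposed cases, a 1:1 comparison and two-sided 5% (assumed). This reproduces Table 1: for 0.9 with 1,200 cases, 0.1054 × √2400 / 2 − 1.96 = 0.62, so power is 0.73, as stated; for 0.8 with 500 cases it gives 0.94, as stated. Then, with no drug effect:

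| Spurious HR | 1,200 cases | 800 | 500 | 200 |
|---|---|---|---|---|
| 0.857 | 0.97 | 0.87 | 0.68 | 0.34 |
| 0.917 | 0.57 | 0.41 | 0.28 | 0.14 |

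The 1,200 column is close to the upper end, because the 1,227 cases in the feasibility count include TB after exposure had ended.

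**The case against.** The best defence is that indication confounds only through a link with TB, and the covariates were chosen for exactly that link. Age, smoking, deprivation, corticosteroids and many comorbidities are compared between starters and are available for adjustment. The protocol also says that local PPI preference followed mainly cost, which speaks against choice by indication, and calendar year is a listed covariate. This stands in part. A reader might infer that such confounding would be neither seen nor removed, or that no gastroprotection-related drug is considered. The documents support neither reading, since much of the pathway is covered and corticosteroids are listed.

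The control outcomes also count. MI should respond to an imbalance in cardiovascular or antiplatelet indications, and zoster to general frailty and infection risk. But both were added after the TB result was known, the MI analysis excludes patients with a prior MI, and neither can reveal an indication linked to TB but not to the control outcome.

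The illustration is open to challenge too. No documented figure supports its inputs, and it uses prevalence among users while the primary contrast is exposed person-time. A short eradication course contributes only its duration plus 60 days and so carries less weight than its share of starters. These points limit the size, not the gap itself.

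Nor is this detail that could be left to an analysis plan: the protocol sets out both lists, and Amendment 2 refers back to the TB covariate list as a defined set.

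**Conclusion.** The point holds as a gap in how the protocol supports its comparator. The premise of similar underlying health is checked on TB risk factors but not on the reason for the PPI or on NSAID or antiplatelet use. Confounding by indication is not directly tested and only partly removed; the MI and zoster analyses narrow this without closing it.

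The size is unknown. With a TB rate ratio of 2 or 3 that persists after adjustment, 10% against 20% would give 0.92 or 0.86. Smaller imbalances give about 0.92 to 0.99, and the direction could be the reverse. A reader might infer that the reported protective association is explained by indication. The documents do not show this: they give no prevalence by drug and no indication-specific TB risk, and only a large imbalance joined to a strong TB link would produce 0.8 by itself. This is a cheap and worthwhile improvement to the design, not a demonstrated bias.

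**What to change.** - **Baseline table (Data/Statistical analysis).** Add indication at first PPI, from GP records around the index date: reflux, ulcer or dyspepsia, H. pylori eradication course (a PPI with the antibiotic combination), GI bleed or upper GI cancer, none recorded. Add NSAID and antiplatelet co-prescription.
- **Sensitivity analysis 1.** Add these variables to the adjusted Cox model, with none recorded as its own category so that no patients are lost.
- **Sensitivity analysis 2.** Exclude patients whose first PPI was part of an eradication course.
- **Labelling.** Because the TB result is already known, mark all of these as post hoc and leave the primary model as it is.

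The cost is a few code lists in the same primary care records, some table rows and two model runs. The downside is that indication is incompletely coded: the none-recorded group may be large and control will be partial, so a hazard ratio that does not move would reassure without settling the matter.
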